### Chart audits

Using a previously successful approach with community ED studies [57], we will ask local medical records departments to pull relevant charts using International Classification of Diseases-10 (ICD-10) codes for all diagnoses related to our index conditions (asthma and V&D) during the defined study periods. Chart auditors will review all records to ensure eligibility criteria are met. All retrieved and eligible patient charts will be audited. Based on data from previous work, and pediatric asthma visits in Ontario EDs [58], we estimate an average of 85 Asthma and 115 V&D patient charts per site during each nine-month pre- and post-intervention period. Therefore, at each site 200 charts will be audited in each period, for a study total of 6,400 chart audits. In the event of multiple visits for the same patient, data will only be collected for the index visit. Four health record auditors will be trained to abstract data from patient records and directly enter these into a secure online database. To assess inter-rater agreement, pairs of auditors will initially each abstract the same 100 charts (50 asthma, 50 V&D). Agreement will be measured with a kappa coefficient and further training will be done until a kappa >0.8 is achieved. A data dictionary will be created to guide the chart auditors and ensure standardized data collection procedures. Auditors will be blinded to the study aims, study design, and group allocation.

### Administrative data

Health administrative databases available at the Institute for Clinical Evaluative Sciences (ICES) will be used to study the impact of being on a CP on overall ED length of stay (LOS), hospital admissions, return visits within 72 hours following ED discharge for non-admitted patients, and death. Appropriate procedures will be used to link health administrative and patient specific data. The relevant databases are National Ambulatory Care Reporting System (NACRS), containing data from all Ontario EDs, and vital statistics data. Only data elements known to be reliable and valid will be used [59]. Use of NACRS data allows efficient capture of return visits, irrespective of whether the patient returns to the index hospital. These data also allow evaluation of shift-level characteristics, such as mean triage adjusted total LOS of all other patients in the ED on the same shift, which is an important contextual variable that may be associated with whether a CP was used and can be used to adjust for the LOS of the study patients. We will model whether the intervention had an impact on EDLOS, hospital admissions, return visits within 72 hours, and death; and whether ED busyness is associated with patients not being put on a pathway [66]. We will control for age, gender, Canadian Triage Acuity Scale (CTAS) rating, and EDLOS for other similar rated CTAS patients.

### Sample size calculation

We conducted sample size calculations for our primary clinical outcome measures using standard formulas for comparing two proportions in cluster-randomized trials [60]. We conducted separate calculations for each CP and selected the larger of the two requirements as our target sample size. We assumed an intracluster correlation coefficient (ICC) of 0.01. This was the largest ICC based on preliminary data from a similar, not yet published study, which showed ICCs for dichotomous outcomes ranging from 0.001 to 0.01. Based on preliminary data, we assumed proportions of 10% in the control arm. We anticipated average numbers of asthma and V&D patients per hospital over the nine-month study duration of 85 and 110 respectively. After applying 10% inflation to account for cluster size imbalances, and allowing for attrition of one hospital per arm, eight hospitals are required in each study arm to yield 90% power to detect an absolute difference of 10% between study arms (10% in the control arm versus 20% in the intervention arm) using a two-sided test at the 5% level of significance. At recruitment, hospitals will be asked for written commitment to the study. Regardless of whether full implementation at that site has been completed, all relevant patient charts will be audited as per the protocol described. Therefore, barring exceptional circumstances, it is unlikely that hospitals will be lost to follow-up.

### Analysis

#### Quantitative analysis

Corresponding to the incomplete block design, separate analyses, as described below, will be carried out for each CP. We will use descriptive statistics to compare hospitals and patient characteristics between the study arms: means and standard deviations will be calculated for continuous variables (or medians and interquartile ranges in the case of skewed distributions) and frequencies and proportions for categorical variables. Because we have a relatively small number of clusters per arm, the assumptions for mixed-effects logistic regression analyses and Generalized Estimating Equations (GEE) are not satisfied; primary analyses will therefore be carried out using cluster-level data [61].

We will first calculate hospital level summary measures (proportions in the case of dichotomous outcomes, or means in the case of continuous outcomes) in the pre- and post-intervention periods. A simple unweighted mean of the change from pre- to post-intervention will then be calculated for each hospital. The main effect measure for each outcome will be calculated as the difference between the mean changes in intervention and control arms, together with 95% confidence interval. If the distribution of the observed hospital summaries is markedly skewed, a logarithmic transformation will be applied, and the effect measures will be expressed as fold-changes. If descriptive analyses reveal important baseline differences in patient case mix between the study arms, a two-stage procedure will be used consisting of a standard regression analysis to obtain a residual adjusted for the covariates of interest in each hospital; hospital residuals will then be analyzed using the approach described above. Statistical significance will be assessed at the 5% level using a two-sample unpaired *t*-test.

We will conduct exploratory individual-level analyses using GEE to test whether ED busyness is associated with patients not being put on a pathway. Shift busyness will be measured as EDLOS for other similar rated Canadian Triage Acuity Scale (CTAS) patients. This analysis will also include the following individual-level covariates: patient age, condition (asthma, V&D) and CTAS rating.

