Clinical outcomes will be measured through data abstracted from patient records and administrative databases in the 9-month pre and post-intervention periods. Prospective audits of the pre-implementation data are not possible as this period pre-dates the trial beginning. The post-implementation period can be clearly identified and prospective audit collection will therefore be done. Following completed implementation, we have scheduled a three-month settling in period before post-intervention audits will commence.

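### The stated 90% power belongs to a post-period comparison of two proportions, not to the planned t-test on hospital-level change, which is the less efficient use of the same baseline data

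*Protocol article*

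**What the plan says.** The *Sample size calculation* section sizes the trial for the primary clinical outcomes "using standard formulas for comparing two proportions in cluster-randomized trials". It concludes that "eight hospitals are required in each study arm to yield 90% power to detect an absolute difference of 10% between study arms", taking "10% in the control arm versus 20% in the intervention arm" and "using a two-sided test at the 5% level of significance". On clustering it says: "We assumed an intracluster correlation coefficient (ICC) of 0.01". It calls this the largest value in preliminary data that showed "ICCs for dichotomous outcomes ranging from 0.001 to 0.01". The figure also carries a 10% inflation for unequal cluster sizes and allows for the loss of one hospital per arm. Neither a pre-period nor a pre-post correlation appears.

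The *Quantitative analysis* section reduces each hospital to a pre-period and a post-period summary and takes the difference. "The main effect measure for each outcome will be calculated as the difference between the mean changes in intervention and control arms", and the test is an unpaired t-test at the 5% level. The only adjustment is conditional and concerns patient case mix, not the hospital's own baseline outcome.

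On timing, the *Outcome measures* section says: "Prospective audits of the pre-implementation data are not possible as this period pre-dates the trial beginning". Post-period audits wait for a further three months after implementation is complete.

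**The concern.** The power statement and the primary test are both fixed in this article, and they do not describe the same analysis. Subtracting the pre-period proportion adds the sampling error of a second, separately sampled set of charts. That pays off only if hospital proportions are strongly correlated between periods. When the two periods have equal variance, a change score beats ignoring baseline only above a correlation of 0.5.

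Two features make a high correlation unlikely. The ICC is small, so most of the variance of a hospital proportion is sampling noise, which does not carry over between periods. The periods are also far apart: the pre-period ends before the trial starts, and post-period audits begin around month 21 (9 + 9 + 3) if the implementation phase runs its full length.

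At stake is whether the trial has the stated chance of detecting a 10-point difference, and whether the baseline data it will collect anyway are put to good use with only 16 hospitals.

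**Working it through.** **Inputs from the article:** 10% v 20%; two-sided 5%; ICC 0.01; 85 asthma and 110 V&D charts per hospital; 10% inflation; eight hospitals per arm, of which seven remain after the allowed loss. **Assumed, not in the article:** the stability *c*, meaning the correlation of true hospital rates between periods, shown from 0 to 1.

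**1. The plan's figure reproduces.** n per arm = (1.96 + 1.2816)² × (0.09 + 0.16) / 0.10² = 262.7 (266 with the pooled-variance formula). Asthma design effect: 1 + 84 × 0.01 = 1.84. Then 262.7 × 1.84 / 85 × 1.1 = 6.26 (6.33 from 266), rounded up to 7, plus 1 = 8. V&D: 266 × 2.09 / 110 × 1.1 = 5.56, rounded up to 6, plus 1 = 7. The larger is eight, as stated, with no pre-period term.

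**2. Post-only power, asthma, seven per arm.** The variance of one hospital's proportion, with the 1.1 factor, is 0.09 × 1.84 / 85 × 1.1 = 0.002143 at 10%, and 0.16 × 1.84 / 85 × 1.1 = 0.003810 at 20%. SE = √[(0.002143 + 0.003810)/7] = 0.0292, and 0.10/SE = 3.43. Power is 92.9% with normal quantiles and 88.2% with a t-test on 12 df. The move from z to t alone takes the figure below 90%.

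**3. Ceiling on the pre-post correlation.** In the control arm, without inflation, the shared between-hospital variance is 0.01 × 0.09 = 0.0009 and the total is 0.09 × 1.84 / 85 = 0.00195. The correlation is at most 0.0009/0.00195 = 0.46, reached only when *c* = 1.

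**4. Planned change-score test, asthma, seven per arm.** Both arms start at 10%. The pre-post covariance is 0.0009*c* in control and 0.01 × √(0.09 × 0.16) × *c* = 0.0012*c* in intervention. The two change variances sum to (2 × 0.002143 − 0.0018*c*) + (0.002143 + 0.003810 − 0.0024*c*) = 0.01024 − 0.0042*c*. At *c* = 0 the SE is √(0.01024/7) = 0.0382 and the ratio is 2.61, giving 67% power. At *c* = 1 the SE is √(0.00604/7) = 0.0294 and the ratio is 3.40, giving 88%.

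**5. Baseline-adjusted analysis (ANCOVA).** With a common slope, the two residual variances sum to 0.002143 + 0.003810 − (0.0021*c*)²/(2 × 0.002143). Multiply by 1 + 1/(2k − 4), the cost of estimating the slope with k hospitals per arm, and use 2k − 3 df. At k = 7 and *c* = 1 this gives 0.00492 × 1.1 / 7, an SE of 0.0278, and 90% power.

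**6. Power (%) at ICC 0.01 with 10% inflation:**

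| Pathway, hospitals per arm | Analysis | c = 0 | 0.5 | 0.8 | 1 |
|---|---|---|---|---|---|
| Asthma, 7 | change score | 67 | 77 | 83 | 88 |
| Asthma, 7 | ANCOVA | 85 | 86 | 88 | 90 |
| Asthma, 8 | change score | 74 | 83 | 89 | 92 |
| Asthma, 8 | ANCOVA | 90 | 91 | 93 | 95 |
| V&D, 7 | change score | 73 | 83 | 90 | 94 |
| V&D, 7 | ANCOVA | 89 | 90 | 93 | 95 |
| V&D, 8 | change score | 79 | 89 | 94 | 97 |
| V&D, 8 | ANCOVA | 93 | 95 | 96 | 98 |

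With eight hospitals per arm, the change-score test reaches 90% at *c* of about 0.87 for asthma and 0.58 for V&D. A beta-binomial simulation without the 10% factor agreed with the corresponding formula results within about one point.

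**The case against.** The strongest reply is that nothing is broken. An unpaired t-test on hospital-level change is valid under randomization and removes additive baseline differences. That stands: no bias is alleged.

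A reader might infer that the planned test falls short of 90% in general. The article does not support that. It gives no pre-post correlation, and it regards the loss of a hospital as unlikely. With all 16 hospitals the test reaches 90% at the stabilities given above. The ICC of 0.01 is also the top of the stated range: at 0.001, asthma power with eight per arm is about 92-94% at any stability. What remains is that the plan chose ICC 0.01 and an allowance for seven hospitals per arm, and on that basis asthma stays below 90% throughout.

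A reader might also infer that baseline adjustment fully recovers the 90%. It does so for asthma with eight hospitals per arm, but with seven only near perfect stability. Part of that gap comes from sizing with normal quantiles and testing on few df. If hospital rates were wholly unstable, adjustment with seven per arm (about 85%) would even trail a post-only t-test (88%).

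The 0.5 threshold assumes equal variances. At 10% v 20% the post-period variance is larger in the intervention arm, so near perfect stability the change score roughly matches post-only. The threshold is a guide; the power table carries the argument.

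Finally, the article applies one method to every outcome, and a baseline covariate cannot serve the primary process outcome. Sites already using either pathway are not recruited, so its baseline is essentially zero everywhere, and subtracting it costs almost nothing. The point is confined to the clinical outcomes.

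**Conclusion.** The concern holds as a matter of precision and of a misstated power figure. The 90% in *Sample size calculation* is not the power of the test in *Quantitative analysis*. For asthma, which sets the sample size, the planned test has about 67-88% power on the plan's own basis and 74-92% if no hospital is lost. For V&D with eight per arm it is 79-97%. ANCOVA was higher in every scenario computed. The gain is large when stability is low or moderate and only a few points when it is near 1.

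These figures rest on ICC 0.01, the article's mean chart counts, a 10% baseline in both arms, the 10% inflation applied to variances, and an assumed range of stability. Applying the inflation to the covariance as well raises change-score power at perfect stability with seven per arm to 89.9%, still short of 90%. If the between-hospital covariance does not grow with the intervention-arm rate, change-score power at perfect stability is about 2-3 points lower (asthma, eight per arm: 89.7%).

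**What to change.** For the two primary clinical outcomes, make the primary analysis a hospital-level linear regression of the post-period proportion on arm and the hospital's pre-period proportion. Base the 95% confidence interval on the number of hospitals minus 3 df (13 with all 16). Keep the difference in mean changes as a sensitivity analysis. Leave the process outcome without this covariate.

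In *Sample size calculation*, restate the power for the analysis that will be run, with t quantiles, for seven and eight hospitals per arm, and over a stated range of pre-post correlation.

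The cost is one degree of freedom, a few sentences, and a somewhat less favourable stated power. No new data are needed, and the article reports that the trial is still in its preparation phase.

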**Design/methods:**

We will develop a theory-based and knowledge user-informed intervention strategy to implement two pediatric clinical pathways: asthma and gastroenteritis. Using a balanced incomplete block design, we will randomize 16 community emergency departments to receive the intervention for one clinical pathway and serve as control for the alternate clinical pathway, thus conducting two cluster randomized controlled trials to evaluate this implementation intervention. A minimization procedure will be used to randomize sites. Intervention sites will receive a tailored strategy to support full clinical pathway implementation. We will evaluate implementation strategy effectiveness through measurement of relevant process and clinical outcomes. The primary process outcome will be the presence of an appropriately completed clinical pathway on the chart for relevant patients. Primary clinical outcomes for each clinical pathway include the following: Asthma—the proportion of asthmatic patients treated appropriately with corticosteroids in the emergency department and at discharge; and Gastroenteritis—the proportion of relevant patients appropriately treated with oral rehydration therapy. Data sources include chart audits, administrative databases, environmental scans, and qualitative interviews. We will also conduct an overall process evaluation to assess the implementation strategy and an economic analysis to evaluate implementation costs and benefits.

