### Outcome measures

Given the nature of our study, both clinical and process outcomes are important to evaluate. Process outcomes relate to use of the CP for relevant patients. Clinical outcomes relate to adherence with key interventions as recommended by each pathway as well as patient specific outcomes. Table 4 presents a description of the specific outcome measures for this study.

**Table 4 T4:** Process and clinical outcomes

**Outcome measure**	**Description**	**Details**
Primary Process Outcome	Completed CP on relevant patient charts	1) Initial: CP started; little or no documentation;
		2) Partial: some but incomplete documentation; or
		3) Full: meets requirements for CP success
Secondary Process Outcomes	CP use based on ED busyness	CP use for relevant patients, adjusted for shift-level ED data [66].
Primary Clinical Outcomes	Proportion of pediatric patients with asthma and V&D who received appropriate treatment, based on CP Key Interventions	Asthma CP: Treatment with corticosteroids [35,36,67,68] in the ED and at discharge, defined as:
		i). Patients with moderate to severe exacerbation are treated with systemic corticosteroids in the ED, and systemic plus inhaled corticosteroids at discharge,
		ii). Patients with mild exacerbation are treated with either inhaled or oral corticosteroids at discharge.
		V&D CP: Appropriate treatment with oral rehydration therapy (ORT), [37,39] defined as:
		i). Patients with moderate to severe dehydration are treated with ORT, and
		ii). Patients with no to mild dehydration are not treated with ORT.
Secondary Clinical Outcomes	Proportion of pediatric patients with asthma and V&D who received appropriate assessment or treatment, based on CP Key Interventions Patient specific outcomes	Asthma CP:
		Documentation of a Pre-school Respiratory Assessment Measure (PRAM) score [69-71].
		V&D CP:
		1) Documentation of a Gorelick score [37] for dehydration; and
		2) Proportion of children treated with intravenous therapy for rehydration [39].
		Both CPs: EDLOS, admission to hospital and re-visits to the ED within 72 hours.

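### The ED-busyness test uses GEE, which the same section sets aside because clusters are few, and no small-sample correction is named

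*Protocol article*

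**What the plan says.** In the Protocol article, Quantitative analysis, the plan notes the small number of clusters per arm, states that "the assumptions for mixed-effects logistic regression analyses and Generalized Estimating Equations (GEE) are not satisfied", and concludes that "primary analyses will therefore be carried out using cluster-level data". Later in the same section it says: "We will conduct exploratory individual-level analyses using GEE to test whether ED busyness is associated with patients not being put on a pathway". The covariates listed for that model are "patient age, condition (asthma, V&D) and CTAS rating". Busyness is a shift-level measure: the length of stay of other patients with a similar triage rating. No standard-error estimator or reference distribution is given.

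Table 4 (Outcome measures) has a single entry under secondary process outcomes, which is pathway use in relation to busyness, described as "CP use for relevant patients, adjusted for shift-level ED data". The Administrative data section also announces the busyness model.

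The section opens by saying that "separate analyses, as described below, will be carried out for each CP". On numbers, the abstract says "we will randomize 16 community emergency departments to receive the intervention for one clinical pathway", and the Sample size calculation says "eight hospitals are required in each study arm to yield 90% power". According to the Control sites section, control hospitals receive no pathway documents.

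**The concern.** The sandwich variance in GEE draws its reliability from the number of independent hospitals, not the number of charts. With few hospitals it tends to be too small, and a z-test built on it rejects too often. The plan recognises this for the primary analyses, then names the same method for the busyness question without saying why the difficulty no longer applies or how it will be handled.

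A hospital can put on a pathway only patients with the condition it is implementing. The informative data are therefore asthma patients at 8 hospitals and gastroenteritis patients at the other 8. Among these patients, condition is fixed by hospital. The plan calls it an individual-level covariate, but in effect it is a hospital-level one.

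At stake is the credibility of one finding: busyness could be reported as a barrier to pathway use on the strength of a standard error that is too small. The trial sets out to identify what makes implementation succeed, so that finding could be carried into later implementation work.

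**Working it through.** **1. The plan's own figure: 8 hospitals per arm.** Inputs from the Sample size calculation: 10% versus 20%, 90% power, two-sided 5%, ICC 0.01, 85 asthma or 110 gastroenteritis patients per hospital, 10% inflation, one hospital lost per arm.

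- Individually randomised size, pooled-variance formula: n = [1.96·√(2·0.15·0.85) + 1.2816·√(0.10·0.90 + 0.20·0.80)]² / 0.10² ≈ 266 per arm.
- Asthma: design effect 1 + 84·0.01 = 1.84; 266·1.84/85 = 5.76; ×1.10 = 6.33; rounded up to 7; plus 1 = 8.
- Gastroenteritis: design effect 1 + 109·0.01 = 2.09; 266·2.09/110 = 5.05; ×1.10 = 5.56; rounded up to 6; plus 1 = 7.

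The larger is 8 per arm, so the stated figure is reproduced. The article gives no error rate for GEE.

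**2. How many hospitals enter the busyness model.** Condition is a covariate and would be constant in a one-pathway model. The covariate list therefore implies one pooled model over 8 + 8 = 16 hospitals. The opening sentence on separate analyses per pathway, if applied here, would give 8 per model. Both readings are shown below.

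**3. Rejection rate with no busyness effect.** Logistic GEE of pathway use on busyness, age and triage rating, plus condition in the 16-hospital model, with independence and exchangeable working correlation. Each setting has about 2,000 to 2,500 simulated trials; Monte Carlo error is √(0.093·0.907/2500) ≈ 0.6 points near the median.

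The following inputs are assumptions, since the article gives none for pathway use: uptake 10% or 40%; between-hospital SD 0.18 to 1.0 on the logit scale; 0 to 100% of busyness variance lying between hospitals; cluster-size coefficient of variation 0.1 to 0.7; a hospital-varying slope (SD 0.3) in some settings. Of the 24 additional settings planned for 16 hospitals, 11 finished and are included; 80% uptake was not reached.

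| Model | Sandwich error, z-test | Mancl-DeRouen error, t on hospitals minus parameters |
|---|---|---|
| 16 hospitals, all 29 settings | 7.2% to 16.1%, median 9.3% | 2.9% to 5.0% |
| of which 0–30% of busyness variance between hospitals (21 settings) | 7.9% to 13.5% | 2.9% to 5.0% |
| of which 50% between (4 settings) | 7.2% to 13.4% | 3.2% to 4.6% |
| of which 100% between (4 settings) | 14.6% to 16.1% | 3.8% to 3.9% |
| 8 hospitals, 18 settings | 11.8% to 24.4% | 1.6% to 3.5% |

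Relative to 5%, the 16-hospital model runs from 7.2/5 = 1.4 to 16.1/5 = 3.2 times nominal, with median 9.3/5 = 1.9. Leaving out the settings where busyness differs only between hospitals, the top is 13.5/5 = 2.7. The 8-hospital model runs from 11.8/5 = 2.4 to 24.4/5 = 4.9 times.

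**The case against.** The strongest defence is that the plan limits its own statement. It ties the difficulty with GEE to clusters per arm and draws a consequence only for the primary analyses. The busyness question is not a comparison of arms, the exposure varies by shift, and the analysis is called exploratory. A stricter method for the randomised comparison and a regression model for an exploratory association is a defensible hierarchy. This lowers the stakes but does not remove the problem: the number of hospitals is still what limits the variance estimate, and the simulated excess persists when most busyness variation lies within hospitals.

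A reader might infer that the plan commits to an uncorrected test. It does not say so. It names no estimator, and an analysis plan that is not shown could specify a correction. The rates in the z-test column are therefore conditional on the standard sandwich error.

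A reader might also take double the nominal error as a minimum, or treat the 8-hospital rates as the expected case. Neither is supported. Double is close to the median for 16 hospitals and the low end is 1.4 times, while the covariate list points to the pooled model. Finally, the hospital-level nature of condition does not mean that a planned test of condition is at risk, because none is planned.

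**Conclusion.** The inconsistency stands as a minor point. Within one section the plan says the assumptions of GEE are not met because clusters are few, then names GEE on the same hospitals for the only secondary process outcome, with no small-sample handling stated. That goes beyond missing detail, because the method is one the plan has itself called unsuitable.

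If the standard sandwich z-test is what is run, the busyness test would reject a true null about 7% to 16% of the time with 16 hospitals, with a median near 9%. The highest rates arise when busyness differs only between hospitals, which is unlikely for a shift-level measure. These figures rest on assumed uptake, site variation and cluster-size spread.

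No primary outcome, randomised comparison or sample size is touched; a reader who inferred a threat to the trial's main conclusions would be going beyond the document. Separately, the secondary label in Table 4 and the exploratory label in the analysis text disagree and need reconciling.

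**What to change.** State the following in the analysis section:

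- **Population.** Post-period patients whose condition's pathway is implemented at their hospital, with both pathways pooled over up to 16 hospitals and condition treated as a hospital-level covariate. Say that the sentence on separate analyses per pathway does not govern this model.
- **Method.** GEE with bias-corrected (Mancl-DeRouen) standard errors and a t reference on hospitals minus parameters. With an intercept and one term each for busyness, age, triage rating and condition, that is 16 − 5 = 11 degrees of freedom.
- **Option.** If the question is whether the same hospital uses the pathway less on its busier shifts, use logistic regression conditional on hospital. This removes stable site differences in uptake and usual length of stay from the busyness coefficient. The condition main effect can then no longer be estimated.
- **Label.** Call the analysis either secondary or exploratory in both Table 4 and the analysis text.

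The cost is a few sentences and a software option. Intervals become slightly wider, and the corrected test is somewhat conservative (1.6% to 3.5% in the simulations) if only 8 hospitals enter a model.
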